### Assessments

2.7

Each patient will participate in the study for at least 6 weeks, starting from the beginning of RT. Demographic and clinical characteristics recorded at baseline will include gender, age, primary tumor location and stage, scheduled treatment, RT dose, and Karnofsky score. Eligible patients will be randomly assigned to the radiology department for functional assessment and intervention.

The study outcomes will be assessed at baseline (2 weeks pre-RT, t0); at the beginning of RT (t1); at 1 (t2), 2 (t3), 3 (t4), 4 (t5), and 5 (t6) weeks; at the end of RT (t7); and at 2 weeks after completion of RT (t8). The schedule of enrollment is shown in Table 2.

**Table 2 tbl2:** Summary of collected data at each time point according to SPIRIT 2013 guidelines.

Period week	Enrollment	Allocation	Treatment						Follow-up
	Week −2	Week 0	Week 1	Week 2	Week 3	Week 4	Week 5	Week 6	Week 8
**Enrollment**									
Eligibility screening	x								
Informed consent	x								
Allocation		x							
Baseline information	x								
**Randomization**		x							
**Intervention**									
CHM group			x	x	x	x	x	x	
Control group			x	x	x	x	x	x	
**Assessment**									
OM onset			x	x	x	x	x	x	x
Intensity of OM			x	x	x	x	x	x	x
Nutritional status		x	x	x	x	x	x	x	
Quality of life		x				x		x	
Safety monitoring			x	x	x	x	x	x	x
**Adverse events** (side effects and complications)			x	x	x	x	x	x	x

CHM: Chinese herbal medicine, OM: oral mucositis, TCM: traditional Chinese medicine.

#### Primary outcome

2.7.1

The primary outcome used in this study will be the onset of OM, intensity of OM and pain. After the start of RT, the patients will be examined daily until onset of OM. Once OM presents, the onset will be recorded in the proforma, and thereafter the degree will be examined weekly until RT is completed and then at 2-weeks post-RT by oncologists.

Subjective assessment of mucositis pain will be performed with a 100-mm visual analog scale (VAS, where 0 = no pain and 100 = worst possible pain) [17], and objective OM grading will be conducted according to the Common Terminology Criteria for Adverse Events, version 5.0 (CTCAE v5.0). The CTCAE v5.0 grades of OM are defined as follows: grade 0, no mucositis; grade 1, asymptomatic or mild symptoms with no intervention indicated; grade 2, moderate pain that does not interfere with oral intake or cause diet adjustment; grade 3, severe pain that interferes with oral administration; grade 4, indication of life-threatening consequences and emergency intervention; and grade 5, death [18].

#### Secondary outcomes

2.7.2

Secondary outcome measures will include nutritional status and health-related QoL.

The nutritional status evaluation indicators will include body weight, body mass index (BMI), albumin, hemoglobin and total lymphocyte count. Weight change will refer to weight loss during treatment. BMI is calculated by dividing body weight (kg) by the square of height (m). Weight change and BMI will be calculated before and after treatment. Blood indexes will be collected during the weekly routine blood and biochemical examinations.

The EORTC Core Quality of Life questionnaire (EORTC QLQ-C30) contains a series of HR-QoL issues related to a wide range of cancer patients. It has been translated into multiple languages and verified for multiple types of cancer, including HNC. It contains five functional scales (physical, role, cognitive, emotional and social), three symptom scales (fatigue, pain and nausea/vomiting), a global QoL scale, and six individual items (dyspnea, insomnia, appetite loss, constipation, diarrhea, and financial difficulties) [19]. The head and neck module (QLQ-H&N35) is a module used for evaluating the HR-QoL of HNC patients. It contains seven multi-item scales for evaluating pain symptoms, swallowing ability, senses (taste/olfaction), speech, social eating, social contact, and sexual behavior. It also includes six single-item scales to investigate the presence of symptoms related to teeth, mouth opening, dry mouth (xerostomia), sticky saliva, coughing, and feeling ill [20]. All scales of the EORTC QLQ-C30 and QLQ-H&N35 range from 0 to 100. A high score on the functional or global HR-QoL scale represents a relatively high/healthy functional level or global QoL, while a high score on the symptom scale represents the presence of symptoms or problems. Patients will complete both questionnaires before, at the 4th week of, and after RT treatment.

#### Safety assessments

2.7.3

No serious AEs are anticipated as a result of the study, and the clinicians will monitor the risks. In cases of AEs caused by anti-cancer treatment or CHM intervention, we will promptly handle the AEs or withdraw the participant from the study. A series of measures to evaluate the safety of the ZYLGS will be monitored throughout the entire trial due to possible herb-induced toxicity. The participants’ blood, liver and kidney function, body weight, and vital signs will be monitored weekly during the treatment period. AEs will be categorized according to the Patient-Reported Outcomes version of the Common Terminology Criteria for Adverse Events (PRO-CTCAE ITEMS Version 1.0) [21] and recorded throughout the study.

For monitoring of the AEs or serious AEs, an independent Data and Safety Monitoring Board (DSMB) review will be conducted for every 50 patients participating in the trial, for a total of four DSMB meetings. A comparative analysis of the incidence of AEs based on the intervention group will be performed at each DSMB review. The DSMB will make recommendations to the research team on appropriate action plans to resolve research safety issues that may arise during the trial. Only when it is determined that an intervention is absolutely necessary for further management of the participants, such as in the event of SAEs, will the research team be un-blinded.

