**Methods:**

A single-center, randomized, two-arm parallel-group, open-label controlled clinical trial will be conducted to determine whether the Zi-Yin-Liang-Ge-San (ZYLGS), which contains *Rx. Scutellariae*, *Rx. Glycyrrhizae*, *Hb. Dendrobii*, *Rx. Ophiopogonis*, and *Hb. Menthae Haplocalycis,* combined with RT can improve the incidence and severity of OM. Two hundred participants will randomly 1:1 to receive at least 6 weeks of RT plus ZYLGS powder or control. The primary outcome measures are onset, gradation of OM (Common Terminology Criteria for Adverse Events v5.0), and oral pain (visual analogue scale). The secondary outcome measures include nutritional status, the EORTC Quality of Life Core Questionnaire and head and neck module. The Patient-Reported Outcomes version of the Common Terminology Criteria for Adverse Events, serious adverse events, and blood and biochemical analysis will be recorded to evaluate the safety. Visits will be performed for each week during the RT treatment period and then 2 weeks in the follow-up period.

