#### Exclusion criteria

2.3.2

The exclusion criteria are as follows:1.Terminal cancer for which aggressive treatments are unsuitable;2.Impaired renal or hepatic function at initial diagnosis (including chronic kidney disease stages III–V and Aspartate transaminase (AST), Alanine aminotransferase (ALT) ≥ 5 × the upper normal limit);3.Uncontrolled psychiatric problems or altered mental status;4.Previous receipt of medications for other clinical trials.

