#### Data analyses

2.8.2

All statistical analyses will be performed by qualified statisticians in SPSS software (SPSS Inc., Chicago, IL, USA; version 13.0) based on the intention to treat (ITT) principle. The data will also be collected and analyzed according to said principle. Continuous variables will be expressed as mean ± SD and compared using unpaired independent *t* tests. Chi-square tests will be used to compare the categorical data between groups.

A two-sided *p* < 0.05 will be considered significant. The trends of change over time in degree of OM, each scale/item of the EORTC QLQ-H&N35 and EORTC QLQ-C30, will be compared between groups with the generalized estimating equation (GEE) in SAS software version 9.4.

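### Adverse events are categorized only by a patient-reported instrument, so symptomless, non-serious laboratory and blood-pressure harms have no stated category in the by-arm comparison at DSMB reviews

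*Protocol article*

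**What the plan says.** Four statements in the protocol article bear on this point.

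- **Categorization.** Section 2.7.3 (Safety assessments): "AEs will be categorized according to the Patient-Reported Outcomes version of the Common Terminology Criteria for Adverse Events". The version cited is PRO-CTCAE Items Version 1.0.
- **Monitoring.** The same section says that participants' "blood, liver and kidney function, body weight, and vital signs will be monitored weekly during the treatment period", and gives possible toxicity from the herbs as the reason. The abstract lists PRO-CTCAE and then adds that "serious adverse events, and blood and biochemical analysis will be recorded to evaluate the safety".
- **Interim comparison.** Section 2.7.3 plans a DSMB review for every 50 patients, four in all, and states: "A comparative analysis of the incidence of AEs based on the intervention group will be performed at each DSMB review".
- **Clinician grading.** CTCAE v5.0 is named in the abstract and in section 2.7.1, both times for oral mucositis only: "objective OM grading will be conducted according to the Common Terminology Criteria for Adverse Events, version 5.0 (CTCAE v5.0".

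The harms expected from the herbs are given in two places. Table 1 lists high blood pressure and hypokalemia among the effects of Rx. Glycyrrhizae. The Discussion repeats both for prolonged use or overdose of that herb and adds metabolic alkalosis. It also links Rx. Scutellariae to liver and lung toxicity.

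**The concern.** A patient-reported instrument records what the patient notices. A harm that is defined by a blood test or a cuff reading, and that causes no symptom, is outside its reach. The article expects harms of this kind from two of the five herbs, but the only scheme it names for categorizing AEs in general cannot hold them.

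What is at stake is the interim by-arm comparison. Treating clinicians see each patient's values and can act on them. Both arms receive radiotherapy and may receive cisplatin, so one abnormal value cannot be put down to the herbs; an excess in one arm can be informative. The DSMB reviews are where the article plans to look for such an excess while patients are still being treated. A rise in liver enzymes or blood pressure on ZYLGS that was neither felt nor serious has no stated route into the incidence compared there.

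The trial is also open-label, so patients' own reports can be affected by knowing their arm. Measured values are less exposed to this, yet they are the ones without a stated category.

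**Working it through.** No power, alpha or event-rate calculation applies, and the article gives no AE incidence to work from. The check sets the statements side by side and counts the harms affected.

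**1. Is another scheme named for AEs in general?** CTCAE v5.0 appears only for oral mucositis. The patient diary in section 2.6 collects reports of adverse effects, but it too is filled in by patients. The laboratory and vital-sign limits in section 2.3 are entry criteria and do not define an AE on treatment. So the answer is no.

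**2. Are abnormal measurements turned into categorized AEs anywhere?** Section 2.7.3 has the values monitored, and section 2.7.2 says "Blood indexes will be collected during the weekly routine blood and biochemical examinations". The abstract lists blood and biochemical analysis beside PRO-CTCAE, not within it. Table 2 has one row for safety monitoring and another for adverse events. No sentence connects the two.

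**3. How many of the Table 1 effects are affected?** Counting each effect once across the five herbs:

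- Rx. Scutellariae: 3 (stomach discomfort; nausea/vomiting; diuresis)
- Rx. Glycyrrhizae: 4 (edema; high blood pressure; hypokalemia; arrhythmia)
- Hb. Dendrobii: 2 (allergic dermatitis; seizure)
- Rx. Ophiopogonis: 5 new ones (allergy; palpitation; flatulence; belching; diarrhea), since nausea/vomiting is already counted
- Hb. Menthae Haplocalycis: 2 (heartburn; headache)

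Total: 3 + 4 + 2 + 5 + 2 = 16. Those that need a measurement are high blood pressure and hypokalemia: 2/16 = 12.5%. This counts arrhythmia as something the patient can feel. If it is not felt, the figure is 3/16 = 18.75%.

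**4. What does the Discussion add?** Metabolic alkalosis and liver toxicity. With the two from Table 1, that makes 4 distinct measurement-defined harms: hypertension, hypokalemia, metabolic alkalosis and liver toxicity. Lung toxicity is not counted, on the assumption that the patient would notice it.

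**5. Which of these events fall through?** Serious ones are recorded separately, and symptomatic ones can be reported by the patient. What remains is the non-serious, symptomless part of these 4 harms. The article gives no means of estimating how often that occurs.

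**6. Does the final analysis cover them?** Section 2.8.2 gives general rules: t tests for continuous variables and, for the rest, "Chi-square tests will be used to compare the categorical data between groups". These could be applied to laboratory and blood-pressure results by arm, but only after all patients have been treated.

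**The case against.** The strongest reply is that the text does not confine the DSMB to PRO-CTCAE items. The sentence on the reviews refers to AE incidence without restriction, and a clinician can record an event and have it counted whatever labelling scheme is used. Section 2.7.3 also has clinicians monitoring risks and handling AEs according to cause, and Table 2 describes adverse events broadly. This stands, and it limits the point to what is stated. The article names a categorization scheme that does not fit some harms it expects, and it does not say how those harms enter the comparison.

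A second reply is that an article may leave AE grading rules to the full protocol or a DSMB charter. That would answer a complaint that no scheme is given. Here a scheme is given, and the problem is its fit.

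Third, the design softens the consequence. The trial is single-center and open-label, so clinicians reviewing the weekly values know the arm, and serious events have their own record. This also stands, and it is why the priority is modest.

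Some stronger readings are tempting but unsupported:

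- A reader might infer that these harms go unmonitored or that the DSMB cannot see them. The weekly checks contradict the first, and nothing in the article supports the second.
- A reader might count all weekly checks as lost data. Those checks are monitoring exposure, not missed events.
- A reader might infer that potassium is not measured. The article does not list the biochemical panel, and a condensed article need not.
- A reader might point to the liver-enzyme entry limit. That is a question of eligibility and does not show a fault in the AE scheme.

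**Conclusion.** The point holds in a limited form. The only scheme stated for AEs other than oral mucositis is patient-reported. Non-serious, symptomless harms defined by a measurement, which the article itself names for the herbs, therefore have no stated category in the AE incidence compared by arm at each DSMB review.

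Its size is 2 of 16 Table 1 effects (3 of 16 if arrhythmia is not felt), or 4 named harms once the Discussion is included. No event frequency can be attached. The likely consequence is a delay, until the final analysis, in noticing a between-arm difference in such events. It is not a failure to measure them.

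The conclusion assumes that categorizing AEs by PRO-CTCAE governs what is counted at the reviews, which is the natural reading but is not spelled out. It does not depend on sample size. Four reviews of 50 fit the 200 participants in the abstract; section 2.8.1 arrives at 40, with which no 50-patient review would be reached, but that conflict is a separate matter.

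**What to change.** In section 2.7.3, replace the categorization sentence with wording to this effect: *AEs, including abnormalities in the weekly laboratory and blood-pressure results, will be graded by clinicians with CTCAE v5.0; PRO-CTCAE will be collected in addition for symptomatic AEs. The by-arm comparison at each DSMB review will include the number of patients with a graded laboratory or blood-pressure AE, shown beside the PRO-CTCAE results.*

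The cost is a short change to one section, some extra grading work, and one more table at each of the four reviews. The values are already collected weekly and the oncologists already use CTCAE v5.0 for mucositis, so no new instrument is needed. For patients already enrolled, results on file can be graded retrospectively.

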### Statistical analysis

2.8

#### Sample size

2.8.1

The sample size estimation was based on the mean difference in the change of the OM intensity from baseline. Based on a previous study, we made the following assumptions in calculating the sample size: a mean difference of 0.9 between the two groups, SD of total score of 0.7, a ratio of 1:1 between the two groups, a two-sided significance level of 0.025 and a power of 0.9 [10]. With these assumptions, a minimum sample size of 34 patients (17 patients in each group) is needed. Considering the estimated 15% dropout rate, the estimated sample size is 40 patients (20 patients per group).

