Each medication in the ZYLGS formula is described in the ancient TCM literature as relatively safe, and in previous meta-analyses, therapeutic doses have been found to cause no significant toxicity in cancer patients [31,32]. However, some serious adverse reactions have been reported from time to time in recent years. For example, it has been reported that prolonged use or overdose of *Rx. Glycyrrhizae* leads to pseudohyperaldosteronism such as hypertension, hypokalemia or metabolic alkalosis, with low serum aldosterone levels [33]. For potential immunoallergic reactions, such as those associated with *Rx. Scutellariae*, which has liver [34] and lung toxicity [35], attention should also be paid to the safe range of medicine usage, the dosage should not be excessive, and the processed products should be selected appropriately according to needs. Despite their sourcing from TCM pharmaceutical factories in Taiwan with Good Manufacturing Practices certification, the safety and herb–drug interactions and toxicity must be monitored.

Our study has some limitations. One is that the research is being conducted in a single center with a small sample size. Second, the study is not a double-blind trial. Third, only short-term observations can be made, so this study cannot produce a long-term prognosis. For example, it will not be possible to predict whether the reduction of side effects of CHM formula will affect the RT cytotoxic effect and thus affect the survival rate.

In conclusion, we have proposed a randomized controlled, open-label, single-center trial to evaluate the efficacy and safety of ZYLGS as a CIM therapy for RT-induced OM. The results of the current research will provide high-quality evidence for assessment of the prophylaxis of RT-induced OM using a TCM-based prescription of ZYLGS.

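### The article gives two unreconciled sample sizes: 200 in the abstract (and implied by the DSMB schedule) and 40 in section 2.8.1

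*Protocol article*

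**What the plan says.** Three places in the protocol article bear on the size of the trial.

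- **Abstract, Methods:** "Two hundred participants will randomly 1:1 to receive at least 6 weeks of RT plus ZYLGS powder or control".
- **Section 2.7.3, Safety assessments:** the independent DSMB "review will be conducted for every 50 patients participating in the trial, for a total of four DSMB meetings". No total is printed here, but four reviews at one per 50 patients make 200.
- **Section 2.8.1, Sample size:** from "a mean difference of 0.9 between the two groups", "SD of total score of 0.7" and "a ratio of 1:1 between the two groups", with a two-sided level of 0.025 and power of 0.9, the article finds that "a minimum sample size of 34 patients (17 patients in each group) is needed". It then allows for dropout: "Considering the estimated 15% dropout rate, the estimated sample size is 40 patients (20 patients per group").

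The Discussion adds, among the limitations, that "the research is being conducted in a single center with a small sample size". It attaches no number, so it settles nothing.

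**The concern.** The abstract and section 2.8.1 print different totals for the same trial, and the DSMB schedule agrees with the abstract. Nothing in the article calls 40 a pilot, a first stage or a subset, and section 2.1 says that the methods stay unchanged throughout.

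Two things depend on which number is true. One is the DSMB: its reviews are triggered by patient count, so a target below 50 produces none. The other is the power statement, which describes only the size for which it was calculated. The trial is also open-label and was already recruiting when the article was written, so a reader needs to know which total was fixed in advance.

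**Working it through.** **Inputs.** From section 2.8.1: difference 0.9, SD 0.7, allocation 1:1, two-sided alpha 0.025, power 0.90, dropout 15%. From section 2.8.2: two-sided alpha 0.05. From the abstract: 200 randomised. From section 2.7.3: one DSMB review per 50 patients, four in all.

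**1. Reproduce the plan's own figure.** The standardised difference is d = 0.9/0.7 = 1.286.

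- Normal approximation: n per arm = 2 × (2.241 + 1.282)² / 1.286² = 15.02, so 16.
- Two-sample t test (noncentral t): n per arm = 16.35, so 17, with power 0.913 at 17.
- Total evaluable: 2 × 17 = 34. After dropout: 34 / (1 − 0.15) = 40.

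Both printed figures, 34 and 40, follow from the stated inputs.

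**2. Can another reading of the inputs give 200?** With the alpha of 0.05 from section 2.8.2, the t test needs 14 per arm. That moves further from 100 per arm, so the difference in alpha between the two sections does not explain the gap.

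**3. Size of the conflict.** 200 / 40 = 5.

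**4. DSMB reviews at each size.**

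| Total randomised | Reviews triggered (one per 50) | Reviews planned |
|---|---|---|
| 40 | 0 (40 < 50) | 4 |
| 200 | 200 / 50 = 4 | 4 |

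**5. Power and detectable difference at each size.** With 15% dropout, 200 randomised leaves 200 × 0.85 = 170 evaluable, or 85 per arm; 40 leaves 34, or 17 per arm. SD is 0.7 throughout, and differences are from the t test at 90% power.

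| Evaluable per arm | Power for 0.9 grade, alpha 0.025 | Detectable difference, alpha 0.025 | Detectable difference, alpha 0.05 |
|---|---|---|---|
| 17 | 0.913 | 0.88 | 0.80 |
| 85 | above 0.999 | 0.38 | 0.35 |

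At 85 per arm the noncentrality is 1.286 × √(85/2) = 8.38, far above the critical value (2.24 on the normal scale), which is why power is practically 1. The normal approximation gives 0.378 and 0.348 for the last row, the same to two decimals apart from rounding at the edge.

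**The case against.** The best defence is that section 2.8.1 calls 34 a minimum and 40 an estimate, so a trial of 200 meets the requirement with room to spare. A journal article also condenses, and the full protocol may hold the reason for 200. Part of this stands. A trial of 200 would be over-powered for a 0.9-grade difference, not under-powered, so its efficacy conclusion is not threatened. The absence of a rationale for 200 is not the finding either. But condensing can drop a reason; it cannot make two printed totals agree. The word minimum belongs to the 34 evaluable patients, while 40 is named as the sample size.

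Three stronger readings are tempting and are not supported.

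- **That section 2.8.1 allows the trial to stop at 40.** It is a sample-size estimate and contains no stopping rule.
- **That safety oversight would vanish at 40.** Section 2.7.3 also provides weekly blood, liver and kidney tests, weight and vital signs, monitoring of risks by clinicians, and recording of adverse events throughout. None of these depends on the total. Only the DSMB reviews would fail to trigger.
- **That the size could be chosen after efficacy results are seen.** No interim efficacy analysis is described, and the DSMB comparison concerns adverse events. Sections 2.1 and 2.2 also give a calendar: about 16 months of recruitment, with the last participant expected in December 2022. That calendar does not say which total is meant (40/16 = 2.5 a month or 200/16 = 12.5 a month, with no accrual rate given). The open-label design leaves some risk, but the article gives no sign that such a choice was made or planned.

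**Conclusion.** The point holds as an internal contradiction and needs correction. The totals of 40 and 200 cannot both be the planned size, and the article does not reconcile them. The arithmetic behind 40 is correct.

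- If 40 is the target, the abstract is wrong and none of the four planned DSMB reviews occurs.
- If 200 is the target, the 90% power in section 2.8.1 belongs to a trial one fifth the size.

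The detectable differences assume the article's SD of 0.7, its 15% dropout and a two-sample t test. The differences of 0.38 and 0.35 are back-calculated from 200. Nothing in the article supports either as a difference that was planned or judged worthwhile, so they describe precision only. The documents do not show which total was approved.

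**What to change.** State the single number that was approved before the first participant was enrolled on 12 September 2021, and use it in the abstract, section 2.7.3 and section 2.8.1. The number should be traced to that approval, not chosen now.

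- **If it is 200:** restate in section 2.8.1 the power or detectable difference for that size, labelled as a description of precision and not as a planned target difference. Use the same alpha as section 2.8.2, since 0.025 and 0.05 now stand side by side. Give the actual reason for 200.
- **If it is 40:** correct the abstract, and reconcile the DSMB triggers with 40 so that the planned reviews can take place.

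In either case, make the correction without reference to accumulating outcome data, and say so. The cost is a wording change and one amendment or published correction; no patients are added to whichever total was approved.
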